Cognition	Secondary Outcome	Cognitive function will be measured using the NIH Toolbox Cognition Battery, which has excellent reliability and validity to measure cognition in young adults and has construct validity among those with TBI. Multiple forms will minimize learning effects. This battery examines 5 cognitive domains (executive function, episodic memory, language, working memory, and processing speed) and takes 20 minutes to complete on a tablet.
Cerebral blood flow (CBF)	Secondary Outcome	Perfusion imaging will be acquired to examine cerebral blood flow.
Metabolomics	Secondary Outcome	Mitochondrial respiration related metabolites, including pyruvate, acetyl-CoA, citrate, isocitrate, alpha-ketogluterate, succinyl-CoA, succinate, fumarate, malate, and oxaloacetate will be assessed on blood samples. The aggregation of all metabolomic data will provide a comprehensive overview of the homeostasis of the participant following repetitive head injury.
Quantitative Susceptibility Mapping (QSM)	Secondary Outcome	Quantitative Susceptibility Mapping of whole brain, as well as regions of interest analysis, will be conducted to inspect the tissue and brain architectural response to head impacts and omega-3 fatty acid supplementation.
Genetic Markers	Exploratory Outcome	Several genetic markers that are known to associate with brain vulnerability will be assessed and regressed against our outcome measures. These genetic markers include, but not limited to, DARC, APOE, KIAA0319, BDNF, TPH2, COMT. Each marker will be compared to the other outcome measures to understand the full effect of the intervention on the genetic markers as a whole.
ADHD	Exploratory Outcome	Participants who meet criteria for ADHD diagnosis will be analyzed to address the interactive effects of DHA+EPA and head impacts in ADHD.

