**Exclusion Criteria**
Are currently pregnant Have had a head or neck injury within the past 6 months Have implanted metal/magnetic devices (e.g., orthodontic braces) Diagnosed with autonomic or cardiovascular disease (e.g., hypertension) Allergy to fish or shellfish Consuming omega-3 FA supplements including plant-based (e.g., flaxseed) in the past 3 months Consume oily fish (>2 servings/month: salmon, bluefin, swordfish, anchovies)

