### Protocol proposal

#### Trial design.

This randomized placebo-controlled trial will consist of 2 groups: (1) DHA+EPA and (2) Placebo (Fig 2). Written informed consent will be obtained from all participants by the study coordinators. If individuals meet inclusion/exclusion criteria, pre-supplement baseline data will be gathered, including demographics, blood spot sample for assessment of omega-3 FA composition, dietary recalls for estimation of antioxidant intake, and symptom checklist. Participants will ingest DHA+EPA or placebo supplements daily throughout the 8-week supplementation phase and the subconcussion intervention phase. Participants in both groups will be required to ingest the supplement while monitored virtually, via Zoom or Facetime. Female participants’ menstrual cycle (MC), as determined by self-report, which will be further validated by salivary progesterone levels, will be monitored during the supplementation phase to determine regular or irregular MC and MC phases. During the biweekly visit, a blood spot sample will be collected to measure DHA+EPA levels and other FAs in the blood. During the subconcussion intervention phase, participants will be fitted with a wrist-worn Actigraph to monitor their activity/sleep levels. The subconcussion intervention will involve performing 20 controlled soccer headings per session. Participants will undergo 2 sessions in a 2-day period. Blood sample, MR data, autonomic reactivity, and clinical measures (symptoms, oculomotor, cognition) will be collected at pre-heading and 24-hour post-1^st^ session, 24-hour post-2^nd^ session, and 7-day post-2^nd^ session. Fig 1 indicates the current status of enrollment and Fig 2 depicts the study flow.

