### Data analysis

#### Primary analysis.

A multivariable mixed-effect regression model (MMRM) will be used to analyze each aim separately to examine the protective effects of DHA+EPA against subconcussive neural injury. As mentioned, the primary time point is set to 24h post-heading. The models will account for repeated measures from the same participants. We expect changes in neurological outcomes (structural, physiological, autonomic impairments, cognition/N-O function) over time to differ between groups, which is reflected in the group (DHA+EPA vs. Placebo) by time (pre- vs. post-heading) interaction. Although we primarily treat time as a categorical variable (pre, 1^st^ 24h, 2^nd^ 24h, 7d, post), we will rerun the model by treating time as a continuous variable (post-heading length) as part of sensitivity analysis. All possible baseline covariates, such as demographics, omega-3 FA compositions, heading kinematics, psychiatric factors, and antioxidant levels, will be evaluated in the context of group difference.

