#### Secondary analysis.

The cumulative effect from 2 heading sessions will be assessed using a MMRM by comparing 2 groups at post-heading time points, especially at 2^nd^ 24h and 168h. The role of female-related factors will be assessed by a series of MMRMs. Using a similar model structure to the primary analysis, sex (male vs. female) will be included as a term to analyze the potential group x sex interaction. We will then focus on female samples in each group to examine the potential phases of the MC (follicular vs. luteal) by group (DHA+EPA vs. placebo) interaction, and estradiol and progesterone levels will be incorporated as predictors. Lastly, the DHA+EPA group data will be stratified to assess whether there are subgroup differences [baseline DHA+EPA deficiency (<4% DHA+EPA) vs. sufficiency (≥4%)] in the outcomes, tested by the model similar to the first MMRM.

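### The baseline omega-3 deficiency comparison uses the DHA+EPA arm only, so it cannot show whether deficiency alters the DHA+EPA effect

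*Protocol article*

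**What the plan says.** The last analysis listed under Secondary analysis in the protocol article concerns baseline omega-3 status. There "the DHA+EPA group data will be stratified to assess whether there are subgroup differences", the subgroups being deficiency (<4% DHA+EPA) and sufficiency (≥4%). The differences are sought "in the outcomes, tested by the model similar to the first MMRM".

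Three other statements bear on it:

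- Primary analysis defines the supplementation effect as a between-arm difference in change over time, "which is reflected in the group (DHA+EPA vs. Placebo) by time (pre- vs. post-heading) interaction".
- Secondary analysis treats two other possible modifiers with both arms present. For the first, "sex (male vs. female) will be included as a term to analyze the potential group x sex interaction". For the second, "We will then focus on female samples in each group to examine the potential phases of the MC", as an interaction with group.
- Trial design places the omega-3 measurement before supplementation and does not limit it to one arm: "pre-supplement baseline data will be gathered, including demographics, blood spot sample for assessment of omega-3 FA composition". The sections on blood fatty acid composition and baseline measures do not limit it either.

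**The concern.** Randomisation protects the comparison of DHA+EPA with placebo. It does not protect a comparison of deficient with sufficient players inside one arm, because those players differ by their own history and diet. If deficient players respond differently to heading whatever capsule they take, the treated arm will show a subgroup difference that has nothing to do with DHA+EPA.

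The protocol's own background makes this plausible. The mouse study described under Preclinical evidence found worse recovery after injury in DHA-depleted than in DHA-adequate animals. That is a difference by baseline status, not by supplementation.

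At stake is a possible report that deficient players gain more, or less, from DHA+EPA, based on a contrast that cannot support either statement. The error can also run the other way: a real difference in benefit can be hidden by an opposing prognostic difference.

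**Working it through.** The protocol gives no power, effect size or subgroup share for this analysis, so there is no stated figure to reproduce.

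**What the contrast estimates.** Write the mean change from pre-heading to 24 hours as follows, where γ is the prognostic difference by deficiency, τ the treatment effect in sufficient players and δ the effect modification:

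| | Sufficient | Deficient |
|---|---|---|
| Placebo | a | a + γ |
| DHA+EPA | a + τ | a + γ + τ + δ |

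- Within-arm contrast (as planned): (a + γ + τ + δ) − (a + τ) = γ + δ.
- Two-arm interaction: (γ + δ) − γ = δ.

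Only the second isolates the change in treatment effect. Once placebo is excluded, no group term remains in a model like the first MMRM.

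**Illustration.**

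- From Sample size: 104 per group and 15% dropout give 104 × 0.85 = 88.4, taken as 88 completers in the arm. Alpha is 0.017. Its sidedness is not stated, and the protocol does not assign it to this analysis.
- Assumed: two-sided test (critical value 2.387), γ = 0.4 SD in both arms, δ = 0, and three possible splits.
- Formula: P(|Z + 0.4/SE| > 2.387), with SE = √(1/n₁ + 1/n₂).

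| Split | n₁ / n₂ | SE | 0.4/SE | Share of trials significant |
|---|---|---|---|---|
| 50:50 | 44 / 44 | 0.213 | 1.88 | 0.305 |
| 80:20 | 17.6 / 70.4 | 0.266 | 1.50 | 0.188 |
| 90:10 | 8.8 / 79.2 | 0.355 | 1.13 | 0.104 |

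Varying γ at a 50:50 split gives about 7% for 0.2 SD, 16% for 0.3 SD and 48% for 0.5 SD.

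**Simulation of both tests** (20,000 runs, 45 per cell, SD 1, two-sided 0.05; γ and δ are assumptions):

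| γ | δ | Within-arm test rejects | Two-arm interaction rejects |
|---|---|---|---|
| 0 | 0 | 4.8% | 4.9% |
| 0.5 | 0 | 65.0% | 5.1% |
| 0.5 | −0.5 | 4.9% | 38.7% |
| 0.8 | −0.8 | 5.0% | 76.6% |

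The second row shows a signal where δ is zero. The last two rows show a real δ that the within-arm test misses.

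**Precision of the two-arm test.** With the same split in each arm, the interaction's variance is twice that of the within-arm contrast, so its SE is √2 ≈ 1.4 times as large. With 90 evaluable per arm (the Aim 1 figure), 90% power at two-sided 0.017 implies a main effect of √(2 × (2.387 + 1.282)²/90) ≈ 0.55 SD. An interaction of that size, tested at two-sided 0.05, has the following power:

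- 50% deficient: SE 0.298, power about 45%; an interaction of 0.84 SD is detectable with 80% power.
- 30% or 70% deficient: SE 0.325, power about 39%; 0.91 SD detectable.
- 90% deficient: SE 0.497, power about 20%; 1.39 SD detectable.

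**The case against.** The strongest reply is that the protocol never says this analysis tests whether deficiency changes the treatment effect. It asks about subgroup differences in outcomes, and a within-arm comparison answers that as a description of treated players. On that reading, finding a true 0.4 SD difference is power, not error. This stands, and the percentages above are therefore not type I error rates for the stated question. They become misleading only if the result is read as differential benefit. That reading is nevertheless likely: the analysis is formally tested with a model like the primary one and follows directly after two modifier analyses.

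A second reply is that Primary analysis already promises to evaluate baseline omega-3 composition in the context of group difference. That shows the variable is not confined to the treated arm, but the sentence names no group-by-omega-3 interaction and is too general to count as one.

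Third, the two-arm test is weak at this sample size. True, and a reason to call it exploratory. It is not a reason to estimate a different quantity.

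Two stronger readings are tempting, and the document supports neither:

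- A reader might infer that the ≥4% group will be small, because Table 2 excludes omega-3 supplement users and people who "Consume oily fish (>2 servings/month: salmon, bluefin, swordfish, anchovies". No baseline distribution is given and nothing ties these exclusions to the 4% threshold, so the split is unknown.
- A reader might infer that the ADHD analysis has the same fault, since "Participants who meet criteria for ADHD diagnosis will be analyzed to address the interactive effects of DHA+EPA and head impacts in ADHD". That row restricts to one subgroup but does not drop placebo, so the randomised contrast is kept. Exploratory Aim 5 already speaks of an interaction.

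**Conclusion.** The point holds as a limit on what the planned comparison can show. The treated-arm contrast estimates prognosis plus effect modification and cannot separate them, and nowhere does the protocol article name a two-arm test of deficiency. This rests on the stated design, not on any assumed number.

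The size is illustrative. The rates of about 30%, 19% and 10% depend on the assumed 0.4 SD prognostic difference, the assumed split and a two-sided 0.017 level. This is a secondary analysis, and the primary comparison is unaffected. The pre-specified 4% cut point is not itself an error; modelling the percentage continuously is an option.

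**What to change.** Include both arms and test group x time x baseline deficiency (<4% versus ≥4%) in a model like the primary MMRM, optionally repeated with baseline DHA+EPA percentage as a continuous term. Report the DHA+EPA minus placebo effect with an interval in each stratum, and label the analysis exploratory. If the within-arm contrast is kept, state that it is descriptive and is not evidence of differential benefit.

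The cost is a change of wording. Baseline status is measured before supplementation with no restriction to one arm, so placebo players can be classified in the same way without new data. The price is precision: the wider standard error and low power shown above, which should be acknowledged when the result is reported.

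### The baseline omega-3 deficiency subgroup is compared within the DHA+EPA arm only, so it does not measure who benefits from supplementation and can point the wrong way

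*Protocol article*

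**What the plan says.** The last item of the Secondary analysis section in the protocol article states that "the DHA+EPA group data will be stratified to assess whether there are subgroup differences". The strata are "baseline DHA+EPA deficiency (<4% DHA+EPA) vs. sufficiency (≥4%)] in the outcomes, tested by the model similar to the first MMRM". With only one arm in the model there is no treatment-group term, so stratum takes its place and the test becomes stratum by time among supplemented players.

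Four other statements bear on this:

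- Primary analysis locates the supplement effect in a between-arm contrast, "which is reflected in the group (DHA+EPA vs. Placebo) by time (pre- vs. post-heading) interaction".
- Earlier in the same Secondary analysis paragraph, two other modifiers are tested against treatment group in both arms. For sex, "sex (male vs. female) will be included as a term to analyze the potential group x sex interaction"; for the menstrual cycle, "phases of the MC (follicular vs. luteal) by group (DHA+EPA vs. placebo) interaction".
- Trial design says "pre-supplement baseline data will be gathered, including demographics, blood spot sample for assessment of omega-3 FA composition", for all eligible participants. Placebo players can therefore be classified by baseline status too.
- Primary analysis lists baseline covariates that include "omega-3 FA compositions, heading kinematics, psychiatric factors, and antioxidant levels, will be evaluated in the context of group difference". This is covariate evaluation; no group by baseline-status interaction is stated.

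**The concern.** A subgroup question about a supplement asks whether the DHA+EPA-minus-placebo difference varies with baseline status. Without placebo players, the analysis shows only how baseline status relates to post-heading change among those supplemented. Players with low omega-3 status may respond differently to heading whether or not they take the capsules, and the planned contrast cannot separate the two. The protocol's own Introduction gives a reason to expect this: it cites preclinical work in which DHA-depleted mice recovered more slowly after injury and had higher levels of axonal-injury markers.

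Three wrong readings are possible: a subgroup effect reported where there is none, no difference reported where deficient players are the ones who gain, or a difference in the wrong direction. Baseline omega-3 status is the modifier most directly tied to the intervention, so a reader will naturally take a deficient/sufficient split of supplemented players as evidence of who should be supplemented.

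**Working it through.** **What the contrast estimates.** Let T and P be mean change from pre-heading to 24 h on DHA+EPA and placebo, with subscripts d (deficient, <4%) and s (sufficient, ≥4%).

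- Planned contrast: T_d − T_s
- Effect modification: (T_d − P_d) − (T_s − P_s)
- Hence planned contrast = effect modification + (P_d − P_s)

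The last term is the prognostic difference under placebo. The two contrasts agree only if it is zero.

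**Inputs.** The Sample size section gives 90 per group for Aim 1, 15% dropout, 104 recruited per group and alpha 0.017. The 104 is matched by 90 × 1.15 = 103.5. After 15% loss, 104 × 0.85 = 88.4, so I take 88 analysed per arm. The plan states no sample size, effect size or power for this subgroup analysis, so it has no figure to reproduce. The following are assumptions: outcome in SD units of change, two-sided tests, the split between strata and the size of the prognostic difference.

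**(a) No effect modification, prognostic difference δ in both arms.** The within-arm standard error is √(1/n₁ + 1/n₂). For 62/26 it is √(1/62 + 1/26) = 0.234. Rejection rates are from the noncentral t distribution with 86 degrees of freedom:

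| Split (n₁/n₂) | δ = 0.3: α 0.05 (0.017) | δ = 0.5: α 0.05 (0.017) |
|---|---|---|
| 50/50 (44/44) | 29% (16%) | 64% (47%) |
| 70/30 (62/26) | 25% (13%) | 56% (39%) |
| 85/15 (75/13) | 17% (8%) | 38% (23%) |

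A group by status test in both arms would reject at its nominal 5% (1.7%). A simulation of 4,000 trials with 90 per arm, a 50/50 split and δ = 0.5 gave 67% rejection for the within-arm test and about 4.5% for the two-arm test at alpha 0.05.

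**(b) Supplementation removes a 0.5 SD deficit in deficient players only.** Take rises in a marker of P_d = 0.5, P_s = 0, T_d = 0, T_s = 0. The planned contrast is 0 − 0 = 0. The true modification is (0 − 0.5) − (0 − 0) = −0.5.

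**(c) Sign reversal.** Take P_d = 1.5, P_s = 0.5, T_d = 0.7, T_s = 0.2. The supplement effects are 0.7 − 1.5 = −0.8 (deficient) and 0.2 − 0.5 = −0.3 (sufficient), so deficient players gain more by 0.5 SD. The planned contrast is 0.7 − 0.2 = +0.5, so they look worse. With 90 per arm and a 50/50 split, the within-arm test was significant in that wrong direction in 65% of 4,000 simulated trials and never in the right one. In a milder case (1.0, 0.4, 0.5, 0.3), the contrast is +0.2 against a true modification of −0.4.

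**Precision of the correct contrast.** Its standard error is √2 times the within-arm one: √2 × 0.234 = 0.330 at 70/30 with 88 per arm. Power for a 0.5 SD interaction is then about 33% at alpha 0.05.

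**Subsidiary: the cut at 4%.** If status is roughly normal, splitting it keeps φ(c)²/[p(1−p)] of the information, where c is the cut in SD units and p the proportion on one side: 64% (50/50), 58% (70/30) or 43% (85/15). One exclusion criterion reads "Consume oily fish (>2 servings/month: salmon, bluefin, swordfish, anchovies", and recent omega-3 supplement users are excluded as well, so unequal strata are likely. The document gives no split.

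**The case against.** The strongest reply is that the plan promises only differences in outcomes between strata. It does not say that the analysis identifies who benefits. Whether supplemented players who started deficient still fare worse after heading is a legitimate descriptive question, and the within-arm contrast answers it. That is true, but the item is tested with the model built to examine the protective effect of DHA+EPA and sits beside two proper interactions with group. As written, nothing marks it as descriptive.

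The magnitudes rest on assumptions. A prognostic difference of 0.5 SD is close to the whole treatment effect implied by the Aim 1 sample size (0.547 SD at two-sided 0.017 and 90% power), and the supporting evidence in the document comes from mice. This stands as a limit on the figures, which is why 0.3 SD is shown as well. It does not touch the algebra.

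It is also fair that this is one secondary item, outside the aims and the outcome table, with no decision rule attached; that a prespecified 4% threshold is easy to interpret, while a continuous term brings a linearity assumption; and that the correct test has low power. These points limit the weight of the finding. Low power is no reason to prefer a more precise estimate of a different quantity. Evaluating baseline omega-3 as a covariate does not supply the missing interaction.

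**Conclusion.** The concern holds. As written, the analysis does not estimate a difference in supplement effect by baseline status, and it departs from how the same section handles sex and menstrual-cycle phase. That conclusion is algebraic and needs no numerical assumption. How far the result misleads depends on how prognostic baseline status is, which the document does not say. For differences of 0.3 to 0.5 SD, splits from 50/50 to 85/15 and 88 per arm, a spurious subgroup finding arises 17% to 64% of the time at alpha 0.05 (8% to 47% at 0.017). Null and reversed results are also possible. The primary analysis is unaffected, so this should be corrected but does not threaten the trial's main conclusions. The choice of a 4% cut and the likely imbalance of strata are secondary, and the conclusion does not depend on them.

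**What to change.** Replace the arm-only comparison with one model fitted in both arms: the primary MMRM plus baseline DHA+EPA by group by time, with its lower-order terms and baseline DHA+EPA preferably continuous. Read effect modification from that term at the 24 h contrast. Report DHA+EPA-minus-placebo effects with confidence intervals at stated baseline levels, including values below and above 4%, and check linearity. If the within-arm comparison is kept, label it descriptive.

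The cost is a change of wording; the blood spots are already collected in both arms. The Fig 1 legend says no participant had reached outcome data collection as of March 2025, so the change can be prespecified if made before outcome data are examined. The price is precision. With 88 per arm and a 70/30 split, the 95% interval for the difference in effect between strata has a half-width of about 1.96 × 0.330 = 0.65 SD. The result should therefore be labelled exploratory, and a non-significant interaction should not be read as an equal effect at all baseline levels.

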#### Blood fatty acid composition.

At baseline and after 8 weeks of supplementation, a fasting capillary blood sample from a fingertip will be collected and sent to OmegaQuant Analytics for blood FA composition analysis [32].

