### Sample size

Based on the sample calculation for each aim, we will recruit a minimum number of subjects needed to conduct all aims. Thus, 208 participants (n=104 per primary group) will be recruited. *Alpha level setting:* The primary groups (DHA+EPA vs. placebo) share 3 post-heading time points (1^st^ 24h, 2^nd^ 24h, 168h), which will be compared to the pre-heading baseline. Thus, we set the alpha level at 0.017 to account for multiple comparisons. Based on the estimated effect sizes and alpha level, a sample size of 90 (Aim 1), 74 (Aim 2), and 82 (Aim 3) per primary group will result in 90% power to detect the supplementation effect. We accounted for a dropout rate of 15%, resulting in n=104 per group needed to accomplish all aims.

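### The secondary analysis by baseline omega-3 status cuts a continuous laboratory value at 4%, which loses power if the relation is a gradient; a continuous term would avoid this at almost no cost

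*Protocol article*

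**What the plan says.** All references are to the protocol article.

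- **The test.** The last item under Secondary analysis says that "the DHA+EPA group data will be stratified to assess whether there are subgroup differences". The classes are "baseline DHA+EPA deficiency (<4% DHA+EPA) vs. sufficiency (≥4" per cent, and the difference is to be assessed "in the outcomes, tested by the model similar to the first MMRM". Only the supplemented arm is used. The only support offered for 4% is the pair of labels, deficiency and sufficiency.
- **The variable.** Under Blood fatty acid composition: "At baseline and after 8 weeks of supplementation, a fasting capillary blood sample from a fingertip will be collected". Each participant therefore has a measured baseline percentage.
- **Other use of the variable.** Under Primary analysis: "All possible baseline covariates, such as demographics, omega-3 FA compositions, heading kinematics, psychiatric factors, and antioxidant levels, will be evaluated". No cut is stated there, and no term is named that would let the supplement effect vary with baseline omega-3.
- **Entry rules that bear on its range.** The exclusion criteria include "Consuming omega-3 FA supplements including plant-based (e.g., flaxseed) in the past 3 months" and "Consume oily fish (>2 servings/month: salmon, bluefin, swordfish, anchovies".
- **Size.** Under Sample size, "208 participants (n=104 per primary group) will be recruited", with 15% dropout allowed for.

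**The concern.** A cut at 4% treats a participant at 3.9% as different in kind from one at 4.1%, and treats one at 4.1% as the same as one at 7%. If outcomes change gradually with baseline status, the comparison of two classes uses only part of what was measured. The result also comes to depend on how many participants happen to lie just above or below the line.

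Two features of this trial sharpen the point. First, the entry rules exclude recent supplement users and regular eaters of oily fish, which should thin the upper end of the range, so the classes may be very unequal. Second, the test uses one arm, so the smaller class could be small in absolute terms.

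What is at stake is the interpretation of a null result. This is the only specified test of whether outcomes differ by baseline status, and a non-significant class comparison could be taken to show that baseline status does not matter when the test had little power to show otherwise. The same section handles a comparable case differently: for the female participants, hormone levels enter as predictors alongside the two-phase comparison.

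**Working it through.** **The plan's own figures.** The article gives no calculation for this subgroup test. Its recruited number reproduces as 90 x 1.15 = 103.5, rounded up to 104 per group. After 15% dropout, 104 x 0.85 = 88.4, so about 88 completers in the DHA+EPA arm. Its alpha is 0.05/3 = 0.0167, given as 0.017.

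**Assumptions, none of them in the article.** Baseline DHA+EPA is roughly normal; the outcome changes roughly linearly with it; a share p lies on one side of 4%. Because p is unknown, a range is shown.

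**Information kept by the cut.** Relative to the continuous value, the kept share is RE = phi(z_p)^2 / (p(1-p)), where z_p is the normal quantile at p and phi the normal density. For example:

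- p = 0.5: 0.3989^2 / 0.25 = 0.637
- p = 0.8: 0.2800^2 / 0.16 = 0.490
- p = 0.9: 0.1755^2 / 0.09 = 0.342

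**Power after the cut.** Take a test that would have 80% power on the continuous scale. This starting value is hypothetical, since the article powers only the supplementation effect. At two-sided alpha 0.05 its noncentrality is 1.960 + 0.842 = 2.802, and power after the cut is Phi(2.802 x sqrt(RE) - 1.960). At two-sided alpha 0.017, replace 1.960 by 2.387.

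| Split | Information kept | Lost | 88 completers count as | Power, alpha 0.05 | Power, alpha 0.017 |
|---|---|---|---|---|---|
| 50/50 | 64% | 36% | 56 | 61% | 58% |
| 70/30 | 58% | 42% | 51 | 57% | 53% |
| 80/20 | 49% | 51% | 43 | 50% | 45% |
| 90/10 | 34% | 66% | 30 | 37% | 31% |

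From a starting power of 90% at alpha 0.05, the four splits give 73%, 69%, 62% and 48%.

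**Sensitivity to the shape of the baseline value** (linear relation kept, loss found by simulation):

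| Shape | 20% below 4% | 50% below | 80% below | 90% below |
|---|---|---|---|---|
| Lognormal, log-SD 0.25 | 62% | 40% | 42% | 55% |
| Lognormal, log-SD 0.5 | 73% | 48% | 39% | 46% |
| Uniform | 52% | 25% | 52% | 73% |

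If the entry rules leave most participants below 4% with a right tail, the lognormal rows at 80% and 90% apply. The loss there is 39% to 55%, somewhat less than the normal model gives for the same splits. If the outcome truly steps at exactly 4%, the loss is zero.

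**Difference detectable between classes.** With 88 completers, 80% power and two-sided alpha 0.05, the standardised difference needed is 2.802 x sqrt(1/n1 + 1/n2):

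- 70 versus 18 (80/20): 2.802 x 0.264 = 0.74 SD
- 79 versus 9 (90/10): 2.802 x 0.352 = 0.99 SD

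These treat the outcome as one change score per person; the repeated-measures model would alter them somewhat.

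**The case against.** The strongest defence is that the authors ask a threshold question. They name a deficient and a sufficient class and fix the boundary in advance, so it is not chosen from the data. If the biology has a step at 4%, the cut is the efficient analysis. That is a fair limit on the finding. However, the article gives no evidence for a step, and a continuous model with a curvature check would still report the estimate at 4%.

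A second defence is that the size of the loss depends on a distribution, a split and a linear gradient that the article does not give. This also stands, so the percentages above are conditional and should be quoted as a range.

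Three stronger readings are tempting, and the document does not support them:

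- **That a real gradient will probably be reported as no difference.** From 80% power at alpha 0.05, detection remains more likely than not at 50/50 and 70/30, is even at 80/20, and falls below one half only beyond that. At alpha 0.017 the balance tips by 80/20. The article does not say which alpha governs this test.
- **That baseline omega-3 is examined nowhere else.** The Primary analysis section lists omega-3 composition among the covariates to be evaluated. What it lacks is a term for effect modification.
- **That removing the cut would show who benefits from the supplement.** Within the DHA+EPA arm alone, even a continuous term shows only how outcome relates to baseline status. Whether the supplement effect varies needs the placebo arm.

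**Conclusion.** The point holds as a minor improvement to a secondary analysis. The only specified test of whether outcomes differ by baseline omega-3 status discards information that the trial will already have. Under a roughly normal value and a linear gradient the loss is about 36% at an even split, 51% at 80/20 and 66% at 90/10. Other plausible shapes give 25% to 73% over the splits examined, and a true step at 4% gives none. A gradient is more easily missed than it needs to be, and a null result would be weak evidence that baseline status is irrelevant. The primary comparison, its sample size and its alpha are not affected.

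**What to change.** In Secondary analysis, make the test of baseline omega-3 status a model with baseline DHA+EPA percentage as a continuous term: linear, with one pre-specified check for curvature. Report the estimate with its confidence interval across the observed range, including at 4%. Keep the below-4% and 4%-or-above classes as a descriptive display.

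State which question is meant. If it is how outcomes vary with baseline status among supplemented participants, the one-arm model can stay, with the continuous term interacting with time. If it is whether the supplement effect varies with baseline status, fit both arms with a group x time x baseline DHA+EPA term, and say openly that this is a different estimand from the one-arm comparison now described.

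The cost is wording only, with no new data, visits or participants. The drawbacks are a linearity assumption, which the curvature check covers in part, and a result shown as a curve instead of two numbers. The legend to Fig 1 states that no participant had reached outcome data collection as of March 2025. On that account the change could have been made then without knowledge of outcomes; if data have since accrued, date the change and state what had been seen.
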